***Study product***

Each participant will receive a supply of SAVVY or placebo along with condoms. Participants will receive supplies in quantities anticipated to last until the next visit. A participant will be instructed to return between scheduled visits to obtain more supplies if needed. A product-dispensing log will be maintained by the clinic and field staff to track all gel products.

***Pelvic* *examination***

A pelvic examination will only be done if the participant has symptoms or a problem that needs to be checked. If a wet mount is positive for *T. vaginalis,* clinical signs or symptoms of a yeast infection with yeast seen on a KOH wet mount, or bacterial vaginosis (Amsel criteria), the woman can be enrolled while starting treatment. Treatment will be recorded on the appropriate DCF and treatment log.

***HIV confirmation at screening and enrollment***

If the OraQuick test is reactive during screening or enrollment, the participant will be told that the test results are preliminary, and a blood specimen will be collected by venipuncture for ELISA and Western blot testing. If one or both of the ELISA and Western blot tests is positive, the woman will be designated HIV positive. Regardless of her final HIV status, however, a woman with a reactive OraQuick result at screening or enrollment will be excluded from trial participation. Women designated HIV-positive will be referred to treatment programs.

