## 3.1 Primary Endpoint

Combined incidence of HIV-1 and HIV-2 infection as determined by detection of HIV antibodies from OMT specimens or by ELISA and confirmed by Western blot and/or PCR.

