# 6.0 EFFECTIVENESS ASSESSMENT

## 6.1 Effectiveness Parameters

The effectiveness of SAVVY against HIV (1 and 2) will be measured by comparing the incidence of HIV antibody detection in the SAVVY group with that in the placebo group.

An incident HIV infection will be defined as follows:

- The presence of HIV antibodies in OMT specimens by OraQuick® rapid test at a follow-up visit, confirmed by Western blot from a dried blood spot specimen, or the presence of HIV antibodies by ELISA and confirmed by Western blot or PCR, and
- The absence of HIV antibodies in OMT specimens by OraQuick rapid test on the sample collected at the previous visit or the presence of an unconfirmed reactive OraQuick result on the sample collected a the previous visit, and
- The absence of a confirmed HIV-positive result for the stored enrollment visit specimen.

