## 6.2 Methods and Timing of Effectiveness Parameters

OMT specimens will be tested for HIV-1 and HIV-2 antibodies at screening, enrollment, and then monthly throughout follow-up using OraQuick (OraSure Technologies, Inc.). OraQuick HIV-1 and HIV-2 is a rapid test device that can detect antibodies to HIV within 20 minutes.

If the OraQuick test is reactive, the participant will be told that the test results are preliminary and a blood specimen will be collected for confirmatory ELISA and Western blot testing, and in some cases PCR testing.

Determination of the study endpoint will differ somewhat according to whether the visit is a typical follow-up visit or a final visit. A final visit can refer to either the 12-month visit or an early discontinuation visit.

a) Prior to the 12-month visit, we will do no additional testing of OMT non-reactive participants. Those participants will be asked to return for their next scheduled visit. Those visits do not appear in the table below.

b) Prior to the 12-month visit, an OMT-reactive participant will undergo additional confirmatory testing with ELISA and Western blot, with PCR as needed. That testing is described in the rows of the table below that begin with an OMT+ result in the left column.

c) At the final visit (12-month or early discontinuation), we will perform ELISA on dried blood specimens from all participants. Depending on the combination of OMT and ELISA results, additional testing may be done (see table).

HIV status for the purposes of the statistical analysis, and participant disposition for the purposes of study counseling, are shown in the table on the next page.

| **Combination of HIV Test Results** | | | | **Participant Disposition1** | **HIV Status for Analysis** |
| --- | --- | --- | --- | --- | --- |
| OMT - 2 | Elisa - | *not done* | *not done* | N/A | HIV - |
| OMT - | Elisa + | WB + | PCR + | N/A | HIV + |
| OMT - | Elisa + | WB - | PCR + | N/A | HIV + |
| OMT - | Elisa + | WB indeterminate | PCR + | N/A | HIV + |
| OMT - | Elisa + | WB indeterminate | PCR - | N/A | HIV - |
| OMT - | Elisa + | WB + | PCR - | N/A | HIV + 3 |
| OMT - | Elisa + | WB - | PCR - | N/A | HIV - |
| OMT + | Elisa - | WB - | *not done* | continue | HIV - |
| OMT + | Elisa - | WB + | PCR + | discontinue | HIV + |
| OMT + | Elisa - | WB + | PCR - | discontinue | HIV + 3 |
| OMT + | Elisa - | WB indeterminate | PCR + | continue4 | HIV + 5 |
| OMT + | Elisa - | WB indeterminate | PCR - | continue4 | HIV - |

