| OMT + | Elisa + | WB - | PCR + | continue4 | HIV + |
| OMT + | Elisa + | WB - | PCR - | continue4 | HIV - |
| OMT + | Elisa + | WB + | PCR + | discontinue | HIV + |
| OMT + | Elisa + | WB + | PCR - | discontinue | HIV + 3 |
| OMT + | Elisa + | WB indeterminate | PCR + | continue4 | HIV + |
| OMT + | Elisa + | WB indeterminate | PCR - | continue4 | HIV - |

1 Disposition prior to the final visit. (First seven rows show 12-month visits, for whom disposition is not applicable.) Women with positive Western blot results should be discontinued from the study and referred to the PEPFAR program for confirmatory testing and management. Women with negative or indeterminate Western blot results should continue and return for the next scheduled follow-up visit and testing.

2 OMT– indicates OMT non-reactive; OMT+ indicates OMT reactive.

3 Repeat WB and PCR.

4 Woman remains in follow-up pending PCR test result.

5 OMT+ / PCR+ may not suffice for a positive diagnosis per country-specific guidelines.

The key test result for determining HIV status will be the Western blot result. Positive Western blot results will be termed HIV-positive, regardless of the PCR test result, although we will repeat testing in women who are Western blot positive and PCR negative. Western blot positive participants will be discontinued from the study and gel use, and referred to the local PEPFAR programs for HIV care. PCR testing will not be the sole arbiter of HIV diagnosis. PCR testing will be done even when Western blot results are positive, however, as discrepant results may be of interest for further analysis.

Prior to the final study visit, participant disposition may differ from the ultimate HIV status because the PCR test result is delayed. For example, a participant may be counseled to continue in the study and return for her next follow-up visit, since she does not yet have a positive Western blot result. But if a delayed PCR-positive result is received some weeks later, she may be designated HIV-positive (footnote 4 in table above). If so, the woman will be notified of her HIV-infected status and referred to PEPFAR. The seroconversion date will be the visit at which the PCR-positive specimen was collected.

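### At screening and enrollment, Section 8.2 labels a woman HIV positive on a positive ELISA even when the Western blot is negative or indeterminate (minor; affects only women already excluded)

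*Protocol*

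**What the plan says.** Section 8.2, under the heading on HIV confirmation at screening and enrollment, orders ELISA and Western blot on venous blood after a reactive OraQuick. It then fixes the label: "If one or both of the ELISA and Western blot tests is positive, the woman will be designated HIV positive". It adds that a reactive OraQuick excludes the woman whatever her final status, and that women designated positive are referred to treatment programs. Section 8.1 speaks of counseling and of referral for support and care.

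Section 6.2 opens with oral-fluid testing at screening, enrollment and monthly. It says that a reactive result leads to blood for ELISA and Western blot and, in some cases, PCR. It then turns to visits after enrollment: "Determination of the study endpoint will differ somewhat according to whether the visit is a typical follow-up visit or a final visit". For these it gives a table of result patterns and the principle "The key test result for determining HIV status will be the Western blot result".

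The endpoint texts do not let an ELISA stand alone. Section 3.1 has "detection of HIV antibodies from OMT specimens or by ELISA and confirmed by Western blot and/or PCR", and Section 6.1 has "the presence of HIV antibodies by ELISA and confirmed by Western blot or PCR".

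**The concern.** The words on one or both tests make a positive ELISA sufficient, so a discordant Western blot is disregarded. The same pattern in an enrolled woman is not accepted as a diagnosis until PCR is positive. Footnote 1 of the Section 6.2 table says "Women with negative or indeterminate Western blot results should continue and return for the next scheduled follow-up visit and testing", and the end of Section 6.2 asks the PEPFAR laboratory for confirmatory testing when a probably infected woman has hard-to-interpret results. For the excluded woman, Sections 8.1 and 8.2 state referral but no request for a retest.

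The looser label gains the trial nothing, because the reactive OraQuick has already excluded her. Its possible cost is that an uninfected woman is told she is HIV positive on evidence that the protocol treats as unresolved in a participant.

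**Working it through.** The plan states no figure on this point, so the check sets the two rules side by side for a woman whose oral-fluid test (OMT) is reactive.

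| ELISA | Western blot | Section 8.2 | Section 6.2 table (OMT reactive) | Rows in 6.2 |
| --- | --- | --- | --- | --- |
| + | + | HIV positive | HIV+ whatever PCR shows | 2 |
| + | − | HIV positive | HIV+ if PCR+, HIV− if PCR− | 2 |
| + | indeterminate | HIV positive | HIV+ if PCR+, HIV− if PCR− | 2 |
| − | + | HIV positive | HIV+ whatever PCR shows | 2 |
| − | − | not designated positive | HIV− (PCR not done) | 1 |
| − | indeterminate | not designated positive | HIV+ if PCR+ (cautioned by footnote 5), HIV− if PCR− | 2 |

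1. **Pairs.** There are 2 × 3 = 6 pairs. Section 8.2 designates 4 as HIV positive, and 2 of those 4 have no positive Western blot.
2. **Rows.** The OMT-reactive rows number 2 + 2 + 2 + 2 + 1 + 2 = 11. The two discordant pairs fill 4 of them: 2 are HIV+ (PCR positive) and 2 are HIV− (PCR negative). So in 2 of 11 rows Section 8.2 says positive where Section 6.2 says negative. One row differs the other way (ELISA negative, Western blot indeterminate, PCR positive).
3. **After the fix below, where PCR is available.** Positive now means Western blot positive, or ELISA positive with PCR positive. No row is then designated positive that Section 6.2 calls HIV−. The one row that differed the other way is left as it is. Agreement rises from 11 − 2 − 1 = 8 rows to 10 of 11. Where no PCR result exists, the two discordant pairs become inconclusive.

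**How often would the label be wrong?** The document gives no prevalence or test accuracy, so this is an illustration on assumed values. Assumptions: prevalence p from 0.02 to 0.10; sensitivity 0.99 for OraQuick and for ELISA; specificity s of each from 0.98 to 0.995; a fraction m from 0.01 to 0.05 of infected women with a non-positive Western blot; 0.99 of uninfected women with a non-positive Western blot; independent errors. Let a = p × 0.99² and b = (1 − p)(1 − s)². The chance that a woman reactive on both tests with a non-positive Western blot is infected is a·m / (a·m + 0.99·b).

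- Lowest (p = 0.02, s = 0.98, m = 0.01): a = 0.019602, b = 0.000392; 0.00019602 / (0.00019602 + 0.00038808) = 0.336.
- Highest (p = 0.10, s = 0.995, m = 0.05): a = 0.09801, b = 0.0000225; 0.0049005 / (0.0049005 + 0.000022275) = 0.995.

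The range is too wide to say how often the label would be wrong. If false positives on OraQuick and ELISA tend to occur in the same women, the chance of infection is lower than shown.

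**The case against.** The strongest reply is that the two rules serve different purposes. Sections 3.1, 6.1 and the Section 6.2 table define a study event in an enrolled woman, where a false positive corrupts the efficacy count. Section 8.2 sorts women who are already excluded, where failing to refer an infected woman is the costly error. A sensitive referral rule can coexist with a specific endpoint rule. The woman is also already reactive on two tests from two specimens, and under many assumed inputs she is probably infected. Footnote 1 describes referral to PEPFAR, even for women with a positive Western blot, as including confirmatory testing, so the program may well retest her.

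Much of this stands. The rules apply at different visits, so they do not contradict each other, and prompt referral is right. But referral does not require a definitive label, and Section 8.2 neither names PEPFAR nor asks for a retest.

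A reader might infer that the protocol has no confirmatory step at screening at all. It does not support that: ELISA and Western blot are themselves the confirmation of OraQuick, and the opening of Section 6.2, which covers screening and enrollment, allows PCR in some cases. The gap is that Section 8.2 gives PCR or retesting no role when ELISA and Western blot disagree.

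**Conclusion.** The point holds and is minor. Section 8.2 designates two result patterns HIV positive without a positive Western blot, and Section 6.2 calls both HIV− when PCR is negative. The size is 2 of 6 pairs, or 2 of 11 table rows. It cannot be turned into a number of women.

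A reader might also infer that the looser rule admits the wrong women or distorts the endpoint. The documents rule that out. Every reactive OraQuick excludes, and the endpoint in Section 6.1 relies on a confirmed result from the stored enrollment specimen, not on this designation. Eligibility, endpoint, event count, power and analysis are unaffected. Only the counseling and referral of excluded women are at issue. The conclusion rests on the text alone; the assumed accuracies serve only to show that the rate of mislabelling is unknown.

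**What to change.** Amend the designation sentence in Section 8.2 and the matching counseling text:

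- Designate HIV positive on a positive Western blot, or on a positive ELISA with a positive PCR where PCR is done as Section 6.2 allows. Requiring the ELISA respects the statement in Section 6.2 that PCR is not the sole arbiter, and the caution in footnote 5.
- If ELISA is positive, the Western blot is negative or indeterminate and no PCR result is available, tell the woman that the result is inconclusive. Refer her at once with a request for confirmatory testing, as the end of Section 6.2 does in follow-up. Do not hold the referral for PCR.
- If PCR is done and negative, follow the Section 6.2 table (HIV−).
- Keep the exclusion of every OraQuick-reactive woman.

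The cost is one amended sentence and revised counseling wording. A few excluded women will receive an inconclusive result and need a retest by the referral program. Sample size, eligibility, endpoint and analysis do not change.

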## 8.3 Follow-up Visits

Monthly follow-up visits are scheduled throughout the study follow-up period on the same date as the participant’s enrollment date (i.e., on the monthly “anniversary” of the enrollment date), and not the date of her last visit. Acknowledging that it will not always be possible to complete follow-up visits on the targeted dates, visits may be completed within a 30-day window around the target date (i.e.,  15 days from the target date). For participants who do not complete scheduled visits within the allowable window, the visit will be considered “missed” and the appropriate DCF will be completed to document the missed visit.

Each participant will have a follow-up visit at an outreach office site convenient for her. Each outreach worker will be assigned to a site and will use the site as a base of operation. The outreach worker is responsible for monthly counseling, interviewing, re-supplying the participants with products, testing for HIV and pregnancy, and, if necessary, home visits to ensure that each participant completes the study. Activities at the monthly visit include:

- A questionnaire will be administered to collect information on use of gel and condoms, and any medical symptoms
- Participants will be counseled about gel and condom use
- Participants will be re-supplied with gel and condoms in an amount sufficient to last until the next follow-up visit
- Participants will provide an OMT specimen for HIV testing
- Participants will give a urine sample for pregnancy testing

If at any visit, the staff person or the study participant thinks that a pelvic examination is necessary or that an AE has occurred, study staff will refer the participant to a study clinic for an examination by a study nurse or a study physician. Also, each participant will be scheduled for a clinic visit at 6 months to perform STI and microbiology testing, and to receive a pelvic examination. If confirmatory HIV testing is needed, the participant will be referred to the clinic for blood collection.

Finally, the participant’s final or discontinuation visit will preferably be done at the clinic. An acceptability questionnaire will be administered and a blood specimen will be collected for HIV status confirmation. Participants will be asked to return to the clinic after their final visit for HIV test results. In some cases, a participant may be asked to return to the clinic for additional testing after 12 months if the HIV results remain unclear.

**STI**

Whenever a curable STI is diagnosed, treatment will be given to the participant and recorded on the DCF. If one of the laboratory tests is positive without clinical evidence of an STI and/or if a prescribed treatment has to be adjusted after laboratory results become available, the participant will be contacted and treated if necessary (study product can be continued). Where possible, the participant’s partners will be referred for treatment.

## 8.4 Interim Contacts and Unscheduled Visits

The participant or the Investigator may request an interim contact or an unscheduled visit at any time during the study. All interim contacts and unscheduled visits will be documented in the participants’ study records and on applicable DCFs.

When an interim contact or unscheduled visit occurs in response to AEs experienced by study participants, study staff will assess the reported event clinically and provide or refer the participant to appropriate medical care. All AEs associated with genital symptoms will be evaluated according to the pelvic exam procedures described for follow-up visits and other procedures as deemed necessary by the Investigator, and diagnosis and follow-up of any observed abnormalities will proceed according to the procedures described there and in the “Adverse Events” section.

Interim visits are distinguished from adverse event visits in that no health-related reaction, effect, or abnormality is reported. Some examples of reasons for an interim visit are:

- To get more product or condoms
- To ask questions of study staff
- To discuss problems with study compliance
- To report the outcome of a pregnancy conceived during the study
- Interim examination – e.g., an examination requested with no complaints or symptoms.

# 9.0 STATISTICAL SUMMARY

## 9.1 Study Size Justification

A two-sided log-rank test with an overall sample size of 2,142 participants (of which 1,071 are in the SAVVY group and 1,071 are in the placebo group) achieves at least 80% power at a 0.05 significance level to detect a 50% reduction in the HIV infection rate if the rate of infection in the control group is 5/100 person-years and loss to follow-up is at most 20% in both groups. These calculations were conducted using the PASS 2000 software, which assumes exponential models for the times to HIV detection and losses to follow-up. Approximately 66 total HIV infections are required to achieve the desired power.

## 9.2 Analysis Plan Summary

A detailed analysis plan that covers both the final analysis and the planned interim analysis will be developed and approved prior to the initiation of the study. The following is a summary of the planned analyses. Any deviations to be made from this summary plan will be documented in the detailed analysis plan.

All primary and most secondary analyses will be conducted on an intent-to-treat basis. However, in order to assess the effectiveness and safety of SAVVY among those participants who complied with key aspects of the study protocol and to evaluate the potential impact of treatment on loss to follow-up, various additional analysis populations may be defined in the detailed analysis plan prior to study initiation. Any key decisions regarding the timing of outcomes, the appropriateness of test statistics or model assumptions, or any other statistical issues will be made in a masked review of the data (i.e., masked to the true randomization groups). Unmasking with respect to the true randomization groups will only be done for the final interpretation of the results, unless otherwise required by the data monitoring committee (DMC) (see section 10.2).

### 9.2.1 Analysis of effectiveness outcomes

The effect of SAVVY on the time to HIV detection will be determined using two one-sided log-rank tests stratified by site. The type one error rate for the one-sided test with alternative hypothesis that SAVVY protects against HIV acquisition will be carried out at the 0.025 level and adjusted to account for the interim analysis described below.[[1]](#footnote-2) Secondarily, proportional hazards regression models will be used to estimate the hazard rate ratio, along with a 95% confidence interval, comparing the SAVVY group to the placebo group for the HIV outcome, controlling for site and any important baseline prognostic variables. A list of the baseline prognostic variables to be included in the models will be provided in the detailed analysis plan prior to study initiation. The homogeneity of the treatment effect across sites will be investigated by introducing a treatment-by-site interaction term to the model. Crude incidence rates, rate ratios, and 95% confidence intervals will be calculated and will be based on the ratio of the number of new infections to the total length of treatment exposure in the interval. Time to HIV detection, in days, will be computed as the difference between the date of HIV detection, estimated using the midpoint between the dates of the first positive HIV test and the preceding negative HIV test, and the enrollment date, plus one.

In addition to the primary analysis, Investigators have an interest in comparing pregnancy rates between the SAVVY and placebo groups. Crude pregnancy rates and corresponding 95% confidence intervals will be calculated by randomization group, and stratified by contraceptive method used at baseline. Outcomes of all pregnancies that occur will be ascertained on worksheets designed for that purpose (see Protocol Addendum, p.37). No hypothesis tests regarding pregnancies are planned. Because this is not a study of the contraceptive effectiveness of SAVVY and because participants will not be discontinued after they develop a desire to become pregnant during the study, any results regarding this outcome will be interpreted with extreme care.

### 9.2.2 Analysis of safety outcomes

On a quarterly basis throughout the trial, adverse events will be coded using the MedDRA system in a collaborative effort by the study clinician and data management staff. The AEs will be summarized by body system and pooled over treatment arms (i.e., completely blinded). Prevalence and incidence rates, pooled over treatment arms, will be calculated for certain important or interesting AEs or groups of AEs (to be determined in collaboration with the project leader and study clinician). These summaries will be used for monitoring purposes only.

